**Methods/design:**

This is a single-centred randomized controlled intervention trial (prospective) comparing standard-of-care with standard-of-care plus a mobile phone-based SMS intervention for 6 months. A total of 216 participants with newly diagnosed type 2 diabetes will be recruited. Data will be collected at the outpatient department of Bangladesh Institute of Health Science (BIHS) hospital at baseline and after 6 months. The primary outcome measure will be change in HbA1c between baseline and 6 months. The secondary outcome measures are self-reported medication adherence, clinic attendance, self-reported adoption of healthy behaviours, diabetes knowledge, quality of life and cost effectiveness of the SMS intervention. The inclusion criteria will be as follows: diagnosed as patients with type 2 diabetes by the BIHS physician, using oral medication therapy, living in Dhaka city, registered with the BIHS hospital, using a mobile phone, willing to return for follow up after 6 months and providing written informed consent. Participants will be allocated to control and intervention arms after recruitment using a randomization software. Data will be collected on socio-demographic and economic information, mobile phone use and habits, knowledge of prevention, management and complications of diabetes, self-perceived quality of life assessment, self-reported diseases, medical history, family history of diseases, medication history, medication adherence, health seeking behaviour, tobacco use, physical activity, diet, mental health status, life events and disability, anthropometric measurements of weight, height, blood pressure and blood tests for HbA1c.

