### Research objectives

The objectives of this study are to:1) Study the effect of mobile phone SMS on medication adherence and control of newly-diagnosed type 2 diabetes in an urban area of Bangladesh; 2) Test the use of mobile phone SMS as clinic appointment reminders and for building awareness about diabetes and its complications; 3) Measure the impact of mobile phone SMS on quality of life of diabetes patients in Bangladesh and 4) Evaluate the cost effectiveness of a mobile phone SMS intervention.

The results of the study will help the policy-makers to understand the importance of creating healthcare systems that better meets the needs of people and develop prevention and management strategies for diabetes and other chronic disease using innovative mobile phone technologies at the national level which can be replicated in other developing countries as well.

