### Hypothesis

Our primary hypothesis is that mobile phone SMS intervention is superior in reducing HbA1c in newly diagnosed type 2 diabetes compared to standard care. Secondary hypothesis is mobile phone SMS will increase diabetes knowledge, medication adherence and clinic attendance better in the interventions group than in the control group. The third hypothesis is participants in the mobile phone SMS group will have a better quality of life than participants in the control group. The fourth hypothesis is that mobile phone SMS will be a cost-effective measure for glycaemic control.

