### Primary outcome measures

[Time Frame: 6 months]Disease progression (HbA1c level).

The primary analysis will be intention to treat which will provide relative unbiased comparisons among the intervention and control groups. It will also reduce the effects of crossover and dropout, which may break the random assignment to the treatment groups in a study.

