### Secondary outcome measures

[Time Frame: 6 months]Diabetes knowledge (questionnaire)Self-reported medication adherence (Questionnaires)Clinic attendance (Clinic registers and questionnaires)Quality of Life (Self-reported questionnaires)Cost effectiveness of SMS interventions in reducing HbA1c

Description of outcome variables:Socio-demographic and economic information: Data on participant’s age, sex, religion, education, marital status, occupation, income, family size, family income, objects ownedMobile phone use and habits: Owns mobile phone, years of using mobile phone, can read SMS, can send SMS, frequency of sending SMS, monthly expenses for mobile phone and SMS, willingness to pay for SMS health advice/ medication reminder, maximum amount for mHealthKnowledge of prevention, management and complications of diabetes: Levels of knowledge and perceptions of diabetics, Risk Factors for diabetes, knowledge about prevention, management and complications of diabetes.Self-perceived Quality of Life Assessment: We will use EQ-5D tool and other modified tools to assess the Quality of Life for all participants. This questionnaire has been tested and validated to capture the difference in quality of life in chronic diseases patients.Self-reported diseases or disease prevalence: Self -reported information on different diseases and physical disability by the study participants.Medical History: Any known history of diabetics, CVD, hypertension, cancer, hypercholesterolemia, stroke, kidney diseases, other vascular disease, major surgery.Family history of diseases: Family history of diabetes, hypertension, heart diseases, stroke, kidney diseases, cancerMedication history: List of current and past medication taken by the patient, medication for diabetes, average monthly expenditure for medication, transportation to health facility/physician and consultation.Medication adherence: We will data on medication adherence of participants using different standardized tools and modifying to local context.Health seeking behaviour: Data will be collected on type of doctor visited during the past year, number of visits, distance travelled for consultation and expenditure for health.Tobacco Use (WHO modified questionnaire): A modified WHO questionnaire on use of different forms of tobacco currently and in the past with expenditure will be recorded.Physical Activity (GPAQ): WHO modified GPAQ questionnaire which has been validated in the fields will be used to capture information on different forms of physical activityDiet (WHO IMS/ Food Frequency Questionnaire): A modified and validated food frequency questionnaire will be administrated to ascertain food consumption pattern and dietary choices, type and frequency of consumption of different foods.Mental health status (PHQ9): The Patient Health Questionnaire PHQ 9 which is a standard tool for collecting mental health status in primary health care setting will be used.Life events and Disability: Life events related questions like new job, marriage, separation, injury, accident will be asked, which will be based on validated questionnaire.Anthropometric Measurements: Weight, Height, Mid-Upper Arm Circumference (MUAC), Waist and Hip circumference, Blood Pressure (BP), Pulse rate.Biological tests: Blood tests for HBA1C will be performed.

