### Data analysis

Data coding, quality control and data entry will be done following established procedures at the International Center for Diarrhoeal Diseases Research, Bangladesh (icddr, b). Precoded questionnaire will be used to minimize data coding errors. All data forms and questionnaires will be checked for errors and necessary corrections will be made before data entry. A data entry programme with built-in range and consistency checks will be used. Frequency distributions will be run to identify outliers. In all analyses, potential confounding variables and effect modifiers will be considered.

Basic presentations of data will include number and percentages of cases with diabetes by age, sex, location of residence, and in relation to different known risk factors. Chi-square tests will be used to assess the association between diabetes and risk factors. Prevalence odd ratios will be calculated for diabetes adjusted for major confounding variables (e.g. age, sex, smoking habits, socioeconomic status, nutritional status, family history of diabetes). Interaction between age and risk factors, obesity and diabetes risk factors, and nutritional status and risk factor (hypertension and diabetes risk factors) will also be examined in the logistic regression model.

Effect of intensive mobile phone SMS intervention will be examined by comparing the longitudinal change in glycated hemoglobin (HbA1c) level changes between intervention and control groups. The change in HbA1C will be defined as the difference between mean HbA1c at the first survey and minus that at the second survey and standardized for the time between surveys. We will analyze the primary outcomes with the t-test. The primary analysis will be intention to treat which will provide relative unbiased comparisons among the intervention and control groups. It will also reduce the effects of crossover and dropout, which may break the random assignment to the treatment groups in a study. Relative risk (RR) will be reported for non-adherence, with an RR less than 1 suggesting better outcome for the intervention group. As a measure of absolute effect size, we will also calculate the number needed to treat (NNT) and its associated 95% CI for both unadjusted primary outcomes. Adjusted analyses by fitting a logistic regression model to the primary outcomes with adjustments for sex, age, baseline HbA1c level will be performed.

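### The analysis section counts two primary outcomes where the rest of the protocol has only HbA1c change, and the second is never named

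*Protocol article*

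**What the plan says.** Outside the analysis section the protocol article is consistent.

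- Abstract, Methods/design: "The primary outcome measure will be change in HbA1c between baseline and 6 months". Self-reported medication adherence is among the secondary measures.
- Hypothesis: "Our primary hypothesis is that mobile phone SMS intervention is superior in reducing HbA1c in newly diagnosed type 2 diabetes compared to standard care". Adherence comes next, at a lower rank: "Secondary hypothesis is mobile phone SMS will increase diabetes knowledge, medication adherence and clinic attendance better in the interventions group".
- Primary outcome measures: one entry, "Disease progression (HbA1c level").
- Secondary outcome measures: the list includes "Self-reported medication adherence (Questionnaires").
- Sample size: the calculation uses only an HbA1c difference, an SD and a two-tailed 5% error level.

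The Data analysis section differs. Its paragraph on the intervention effect begins with HbA1c change and a t-test for the primary outcomes, in the plural. It then says: "Relative risk (RR) will be reported for non-adherence, with an RR less than 1 suggesting better outcome for the intervention group". The next sentence promises to "calculate the number needed to treat (NNT) and its associated 95% CI for both unadjusted primary outcomes". The paragraph ends with a logistic regression on the primary outcomes, adjusted for sex, age and baseline HbA1c. Secondary outcomes are taken up only in the paragraph after that.

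**The concern.** A stray plural can be a slip, but the word *both* counts two. The section that governs the analysis therefore disagrees with the sections that define the outcomes, and it does not say what the second primary outcome is. A later analysis plan or report could follow either count and cite this article for it.

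The rank matters because of the likely candidate. Non-adherence is self-reported, and the Randomization section accepts that participants cannot be masked. It is thus more open to a favourable answer than a laboratory HbA1c measured by masked staff. As a secondary outcome it can be read with that caution. As a primary outcome it could support the trial's main conclusion, and neither the sample size nor the error rate was set for that.

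**Working it through.** **1. How many primary outcomes, section by section**

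| Section | Primary | Rank of adherence |
|---|---|---|
| Abstract, Methods/design | HbA1c change | secondary |
| Hypothesis | HbA1c | secondary |
| Sample size | HbA1c only | not used |
| Primary / Secondary outcome measures | HbA1c | secondary |
| Data analysis | two, second not named | no rank given; relative risk placed before the secondary-outcome paragraph |

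**2. What the second one could be.** The paragraph deals with two outcomes only, HbA1c change and non-adherence. An NNT and a logistic regression need a binary outcome. Non-adherence, reported as a relative risk, is binary. HbA1c change is continuous and has no responder cut-off. The first research objective names the same pair ("Study the effect of mobile phone SMS on medication adherence and control of newly-diagnosed type 2 diabetes"), although it ranks nothing. Against this, a t-test does not suit an outcome reported as a relative risk. No single assignment fits all three uses of the plural.

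**3. The plan's own sample size.** Inputs from the Sample size section: difference 0.5, SD 1, two-sided alpha 0.05, 90 per arm, 20% loss.

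- Power = Φ(0.5/√(2/90) − 1.960) = Φ(3.354 − 1.960) = Φ(1.394) = 91.8% (noncentral t: 91.6%). This agrees with the stated figure of over 90%.
- Total: 180 × 1.2 = 216, as stated. Losing 20% of 108 leaves about 86 per arm, and power is then 90.6%.

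The stated design is thus reproduced with one HbA1c test at the full 5%.

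**4. What a second primary outcome would do.** The rules below are assumptions; the protocol states none of them.

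- Each tested at 5%, either one sufficient: 1 − 0.95² = 9.75% if independent. With an assumed correlation between test statistics of 0.3, 0.5 or 0.8 it is 9.5%, 9.1% or 7.8%. The upper bound under any dependence is 0.05 + 0.05 = 10%.
- Each tested at 2.5%, either one sufficient: HbA1c power = Φ(3.354 − 2.241) = Φ(1.113) = 86.7% with 90 per arm, and 85.0% with 86. For 90% power, n = 2 × (2.241 + 1.282)²/0.5² = 99.3, so 100 evaluable per arm. The same formula at 5% gives 85.
- Both required: the chance of a false claim of success does not exceed 5%.

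**The case against.** The strongest reply is that this is loose drafting. No sentence calls adherence primary, and three places rank it secondary. The single primary hypothesis points to HbA1c as the outcome that decides. The article is free with plurals elsewhere: the heading for the primary outcome is plural over a list of one. Words may also have dropped out, since *both unadjusted* followed by a sentence on adjusted analyses could once have meant unadjusted and adjusted. Much of this stands. It shows that the second primary outcome is unidentified and that HbA1c is probably what was meant. It does not make the paragraph agree with the other sections. On the dropped-words reading, the paragraph still promises an NNT for a continuous outcome.

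A reader might also infer three stronger things that the document does not support.

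- *That the trial plans two routes to success at a 9.75% error rate.* No success rule is given. For non-adherence the paragraph offers estimates (a relative risk and, on this reading, an NNT with its interval).
- *That participants are asked daily whether they took their medication.* The 90 messages are sent in random order, one a day. Of the 15 examples shown, three mention taking medication and one asks about it. The concern about self-report rests on the lack of masking.
- *That the condition for the secondary economic modelling in the Discussion becomes ambiguous.* The primary analyses meant there are most naturally those so labelled under Health economic analysis. Their measures of effect are HbA1c units and EQ-5D, not adherence.

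**Conclusion.** The contradiction holds. The Data analysis section counts two primary outcomes, while every section that defines or sizes the outcomes has one. That non-adherence is the second is the most plausible reading, but it is inferred from the adjacent relative-risk sentence and from the need for a binary outcome. The point does not depend on it: if something else was meant, the plan has an undefined second primary outcome.

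The possible inflation, from 5% to 9.75% under independence and at most 10%, applies only if each outcome is tested at 5% and either suffices. It measures what the ambiguity leaves open and is not a property of a stated plan. The stated sample size is reproduced under the single-outcome reading (91.8% power), so settling on HbA1c requires no redesign. The text should be corrected because it fixes which test supports the trial's conclusion.

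**What to change.** In the Data analysis section:

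1. Replace the plural in the t-test sentence with the single primary outcome, HbA1c change at 6 months, and state that its test alone decides whether the trial succeeds.
2. Move the relative risk and the NNT for non-adherence to the following paragraph on secondary outcomes.
3. Delete the NNT for HbA1c. There is no responder cut-off on which to base one.
4. Attach this paragraph's logistic regression to binary secondary outcomes only. Any adjusted HbA1c analysis should use a linear model with the covariates already listed (sex, age, baseline HbA1c).

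Substituting HbA1c change for the plural throughout would not be enough, because it would leave an NNT and a logistic regression attached to a continuous outcome. The two outcome lists and the Discussion text on secondary economic analyses need no change.

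The cost is a few sentences. No patients, data or power are lost; the only thing given up is the option of resting the main conclusion on adherence. Keeping two primary outcomes instead would mean naming the second, stating a multiplicity rule and redoing the sample size. With alpha split equally, HbA1c alone would need 100 evaluable participants per arm for 90% power.

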Secondary outcomes will be compared with the χ2 test for categorical outcome. Fisher's exact test for outcomes will be used to estimate p values. Logistic regression will be used for Quality of Life (QoL) and other continuous variables. In the subgroup analysis in the intention-to-treat population, we will compare the intervention groups within each subgroup of patients with the χ2 test for the categorical outcome and logistic regression for QoL. For all models, the results are expressed as an estimate of effect size, with 95% CIs and p values. The response type throughout the study period will be analysed by categorising time since random allocation to the 6 months and doing a χ2 test between time and response type. All statistical analyses will be done using SPSS version 20 (IBM Corporation, USA).

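### Logistic regression is prescribed for HbA1c change and quality of life, and an NNT for HbA1c change, although the plan treats these outcomes as continuous and defines no cut-point; the primary t-test is unaffected

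*Protocol article*

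**What the plan says.** **Primary outcome.** The Abstract (Methods/design) states: "The primary outcome measure will be change in HbA1c between baseline and 6 months". The Primary outcome measures section lists HbA1c level and nothing else. Data analysis makes the quantity numeric: "The change in HbA1C will be defined as the difference between mean HbA1c at the first survey and minus that at the second survey", further standardised for the time between surveys. It then says: "We will analyze the primary outcomes with the t-test". The Sample size section assumes a mean reduction of 1 percentage point under standard care, an extra 0.5 from the intervention and an SD of 1.

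**Further analyses of the primary outcome.** The same paragraph of Data analysis plans to "calculate the number needed to treat (NNT) and its associated 95% CI for both unadjusted primary outcomes", and ends: "Adjusted analyses by fitting a logistic regression model to the primary outcomes with adjustments for sex, age, baseline HbA1c level will be performed".

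**Quality of life.** The secondary-outcome paragraph says: "Logistic regression will be used for Quality of Life (QoL) and other continuous variables". It repeats logistic regression for quality of life within subgroups.

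**Diabetes as an outcome.** Earlier in Data analysis, chi-square tests of diabetes against risk factors are planned, and "Prevalence odd ratios will be calculated for diabetes adjusted for major confounding variables". The inclusion criteria admit only patients diagnosed with type 2 diabetes.

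**The concern.** A logistic model as named here needs a two-level outcome, and an NNT needs an event. The plan defines no event for HbA1c or for quality of life. An analyst following the text must therefore either depart from it or create a binary variable by choosing a cut-point.

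An unspecified cut-point can be chosen after the data are seen. It discards information, and it yields an odds ratio that cannot be set beside the mean difference from the t-test.

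What is at stake is the only adjusted analysis named for the primary outcome, the NNT, and the only model named for quality of life, which carries the third hypothesis in the Hypothesis section.

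The word *both* in the NNT sentence adds a second difficulty, because it implies a primary outcome that the outcome list does not contain.

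**Working it through.** **1. The plan's own sizing.** Inputs from Sample size: difference δ = 0.5, SD σ = 1 (taken here as the SD of the change), two-sided α = 5%, 90 per arm.

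Power = Φ(δ / (σ√(2/n)) − 1.96) = Φ(0.5 / 0.1491 − 1.96) = Φ(1.394) = 0.918. The noncentral t gives 0.916. This reproduces the stated power of over 90%, so the trial is sized on a difference in means.

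After the planned 20% loss, 108 × 0.8 = 86.4, or about 86 per arm. Power = Φ(0.5 / 0.1525 − 1.96) = Φ(1.319) = 0.906, or 0.903 by the noncentral t.

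**2. Outcome scale against prescribed method.**

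| Outcome | Scale in the plan | Prescribed | Can it be run as written? |
|---|---|---|---|
| HbA1c change | Continuous | t-test | Yes |
| HbA1c change | Continuous, no threshold | Adjusted logistic regression | No |
| HbA1c change | Continuous, no threshold | NNT = 1 / risk difference | No |
| Quality of life, overall and in subgroups | Called continuous | Logistic regression | No |
| Diabetes status | Present in everyone | Chi-square test, prevalence odds ratio | No |

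As a check, a binary logit was fitted to 180 simulated HbA1c changes (means 1.0 and 1.5, SD 1). The fit was refused because the values lie outside 0 to 1. With an outcome equal to 1 for every participant, the fit was singular.

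**3. What an improvised cut-point would do (illustration only).** Assume normal changes with means 1.0 (control) and 1.5 (intervention) and SD 1, and call a participant a responder if the HbA1c reduction exceeds c. The values of c are assumptions; the protocol gives none.

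For the median split, c = 1.25:
- Control: 1 − Φ(0.25) = 0.401. Intervention: 1 − Φ(−0.25) = 0.599.
- Risk difference 0.197, so NNT = 1 / 0.197 = 5.1.
- Power with 86 per arm, unadjusted two-proportion test: Φ[(0.1974 − 1.96√(2 × 0.25/86)) / √(2 × 0.2403/86)] = Φ(0.642) = 0.739.

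| c | Control | Intervention | NNT | Power, 86 per arm |
|---|---|---|---|---|
| 0.5 | 0.691 | 0.841 | 6.7 | 64% |
| 1.0 | 0.500 | 0.691 | 5.2 | 73% |
| 1.25 | 0.401 | 0.599 | 5.1 | 74% |
| 1.5 | 0.309 | 0.500 | 5.2 | 73% |
| 2.0 | 0.159 | 0.309 | 6.7 | 64% |

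With 90 per arm, the range over the same cut-offs is 66% to 76%, against about 92% for the t-test.

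**4. Number of primary outcomes.** Primary outcome measures lists one. The sentence before the NNT sentence concerns the relative risk of non-adherence, and the first research objective pairs adherence with diabetes control. The missing second outcome may therefore be non-adherence. Secondary outcome measures, however, lists self-reported adherence as secondary.

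**5. Diabetes odds ratios.** At full recruitment there are 216 participants with diabetes and 0 without. The odds in any risk-factor group have a zero denominator, so no prevalence odds ratio exists, adjusted or not.

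**The case against.** The strongest reply is that the confirmatory analysis is sound. The t-test on HbA1c change, by intention to treat, matches the endpoint and the sample size, and the faulty items are supportive, secondary or descriptive. That stands. A reader might infer that the primary result is invalid, or that the trial loses power from 90% to 74%. The documents support neither: the plan proposes no median split, and an added dichotomised analysis would not replace the t-test.

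A reader might also infer that an NNT is planned for quality of life. It is not; the NNT is tied to the primary outcomes only, and quality of life is affected solely through the logistic model.

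Third, if *both* means HbA1c and non-adherence, then relative risk, NNT and logistic regression suit the second of these. That reading is plausible, so the phrase should not simply be struck out. It does not give HbA1c an event, and it conflicts with the listing of adherence as secondary.

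Fourth, quality-of-life scores can be ordinal or bounded, and an ordinal logistic model might suit individual EQ-5D dimensions. The plan, however, names no ordinal model and calls these variables continuous.

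Finally, a separate analysis plan, not shown here, might supply cut-points. It would then be repairing a model that the protocol has already fixed wrongly, so this is more than detail left for later.

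The diabetes odds ratios do not touch the randomised comparison and cannot bias the treatment effect. They are a minor matter.

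**Conclusion.** The point holds in limited form. As written, the adjusted logistic regression and the NNT for HbA1c change, and the logistic regression for quality of life (overall and in subgroups), cannot be run without a dichotomisation that the plan does not specify. The unadjusted t-test on HbA1c change is valid, and its stated power is reproduced.

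The figures of about 74% against about 90%, and an NNT moving between 5.1 and 6.7, show what an improvised threshold could do. They rest on normal changes, the protocol's means and SD, 86 per arm, and cut-offs assumed for this illustration; they are not a forecast of the trial's power.

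The reference to two primary outcomes contradicts the outcome list. The chi-square tests and odds ratios for diabetes cannot be estimated, which is a lesser fault of description.

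**What to change.** - **HbA1c:** replace the logistic model with linear regression (ANCOVA) on arm, baseline HbA1c, age and sex, and report the adjusted mean difference with its 95% CI. The response can remain the change score. If the change is not rescaled for time, the arm coefficient is the same for the change and for the 6-month value once baseline is in the model.
- **Quality of life and other outcomes treated as continuous:** linear regression on arm and the baseline value, reported in the same way, including in subgroups.
- **Binary outcomes:** keep logistic regression, relative risk and NNT for outcomes with a stated definition, such as non-adherence. If an HbA1c responder analysis is wanted, fix its threshold before outcome data are seen.
- **Outcome hierarchy:** reconcile the reference to two primary outcomes with the single one listed, stating whether non-adherence is primary or secondary.
- **Diabetes prevalence text:** replace the chi-square, prevalence odds ratio and related interaction analyses with a table of baseline characteristics by arm.

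The cost is a rewording of the Data analysis section. The covariates for HbA1c are already named, linear models can be fitted in the SPSS package already planned, and no new data or participants are needed.

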### Data collection and intervention

Data will be collected at baseline (0 month) and after 6 months through questionnaires, physical measurements and blood tests (Figure 1). We will send out mobile phone SMS to patients in the intervention group for medication reminders and health education about diabetes, its complications, diet and physical activity. SMS content has been developed using different national and international guidelines for diabetes and will be field tested for clarity and contents. The patients will be encouraged to send messages/call the study team for any queries encountered in response to the text messages. The study team will then call patients who had a problem within 2 working days. Study staff will maintain a study register to record all SMS responses and other mobile phone communications with patients in a study log.

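### No stated comparison of medication adherence or diabetes knowledge uses the outcome's own baseline value, although both are collected before randomisation

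*Protocol article*

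**What the plan says.** **Measurement.** Under Data collection and intervention: "Data will be collected at baseline (0 month) and after 6 months through questionnaires, physical measurements and blood tests". The Secondary outcome measures list includes "Diabetes knowledge (questionnaire" and "Self-reported medication adherence (Questionnaires", with no scale or cut-off for either. The Discussion gives the order of events as consent, interview and blood sample, then allocation, so the baseline answers precede randomisation. The inclusion criteria require current metformin treatment, so there is adherence to ask about at baseline.

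**Hypothesis.** "Secondary hypothesis is mobile phone SMS will increase diabetes knowledge, medication adherence and clinic attendance better in the interventions group than in the control group"

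**Analysis**, all under Data analysis:
- categorical secondary outcomes: "Secondary outcomes will be compared with the χ2 test for categorical outcome. Fisher's exact test for outcomes will be used to estimate p values"
- continuous secondary outcomes: "Logistic regression will be used for Quality of Life (QoL) and other continuous variables"
- non-adherence: a relative risk, where a value below 1 favours the SMS arm
- adjusted model: "Adjusted analyses by fitting a logistic regression model to the primary outcomes with adjustments for sex, age, baseline HbA1c level will be performed"
- general statement: "In all analyses, potential confounding variables and effect modifiers will be considered"

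**The concern.** For each participant who returns, the trial will hold a pre-randomisation value of the outcome being tested. That value is often the best single predictor of the 6-month value. A two-by-two chi-square or Fisher test and a crude relative risk leave it unused. The logistic model could take it, but the article names no covariate there. HbA1c is treated differently: it is analysed as change from baseline, and baseline HbA1c enters the adjusted model.

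Two things are at stake. The comparison may be less precise than the collected data allow. A chance difference between arms at baseline can also carry over, in part, into the 6-month result. Both matter because the Discussion describes the expected mechanism as knowledge leading to adherence and then to glycaemic control. No power is stated for either outcome, so they would carry much of the interpretation if the HbA1c result were unclear.

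**Working it through.** **1. The plan's own figure.** The only stated power is for HbA1c: difference 0.5, SD 1, two-sided 5%, 90 per arm. Power = Φ(0.5·√(90/2) − 1.96) = Φ(1.394) = 91.8% (91.6% with the t distribution). The stated figure of over 90% reproduces. The article gives no rate, effect or correlation for adherence or knowledge, so every input from here on is an assumption.

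**2. Non-adherence as a binary outcome.** Assumed: 50% at baseline in both arms; 50% (control) versus 30% (SMS) at 6 months; 90 per arm; baseline-to-6-month correlation φ. The Background cites an average of 50% for developed countries, but this is not a planning value.

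Unadjusted test: SE under the null = √(2·0.4·0.6/90) = 0.0730; SE under the alternative = √((0.25 + 0.21)/90) = 0.0715. Power = Φ((0.20 − 1.96·0.0730)/0.0715) = Φ(0.80) = 78.7%.

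Simulated power (40,000 trials per setting) of the plain chi-square and of a Mantel-Haenszel test stratified by baseline status:

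| φ | Chi-square | Stratified | Gain (points) |
|---|---|---|---|
| 0 | 79.1% | 78.4% | −0.7 |
| 0.2 | 79.3% | 80.3% | +1.0 |
| 0.3 | 79.2% | 82.1% | +2.9 |
| 0.5 | 79.2% | 89.0% | +9.8 |

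Cross-check by formula: Φ((1.96 + 0.80)/√(1 − φ²) − 1.96) gives about 82% at φ = 0.3 and 89% at φ = 0.5.

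With a smaller effect, 50% versus 35%, the figures are 52.5% versus 56.3% at φ = 0.3 and 53.0% versus 65.2% at φ = 0.5. If 20% of 108 are lost, 108 × 0.8 ≈ 86 per arm remain. For 50% versus 30% the unadjusted power is then 76.8%, and the gains are of the same size.

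**3. Knowledge, if it is a score.** Adjusting for baseline multiplies the variance by 1 − r², so power = Φ(d·√(n/2)/√(1 − r²) − 1.96). With an assumed standardised effect d = 0.42 and n = 90:
- 6-month score alone: 0.42·6.708 = 2.82, power 80.4%
- r = 0.2: 82.0%
- r = 0.3: 2.82/0.954 = 2.95, power 84.0%
- r = 0.5: 2.82/0.866 = 3.25, power 90.2%

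**4. Chance imbalance.** With 50% baseline prevalence and 90 per arm, the SD of the baseline difference is √(2·0.25/90) = 7.5 percentage points. The probability of a gap of 10 points or more in either direction is 2·(1 − Φ(0.10/0.0745)) = 18%. With 50% prevalence at both times, the expected shift in the 6-month difference is φ times the gap: 3 points at φ = 0.3 and 5 at φ = 0.5 for a 10-point gap.

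Simulated false-positive rates with no true effect (50% in both arms):

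| φ | Chi-square, all trials | Chi-square, given a gap ≥ 10 points in one direction | Stratified, same gap |
|---|---|---|---|
| 0.2 | 4.6% | 5.2% | 5.2% |
| 0.3 | 4.5% | 6.6% | 5.3% |
| 0.5 | 4.4% | 10.0% | 5.0% |

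**The case against.** **The analysis plan may settle it.** Only a condensed article is shown, and covariate lists for secondary outcomes are often left to the analysis plan. That would answer a complaint about missing detail. Here, however, the article names the tests, and the comment concerns those tests. The sentence "In all analyses, potential confounding variables and effect modifiers will be considered" leaves room for adjustment. It names no variable, model or outcome, so it does not amount to a baseline-adjusted analysis.

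**Knowledge may not go to chi-square or Fisher at all.** This stands. A reader might infer that both outcomes are tested that way, but the article gives no scale for knowledge. A score would fall under the logistic regression sentence. That sentence names no baseline term either, so the gap is the same on both readings.

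**The adjusted model may cover non-adherence.** A reader might infer that it covers neither outcome, because HbA1c is the only listed primary outcome. But the text just before the model speaks of two primary outcomes in connection with the number needed to treat, straight after the relative risk for non-adherence. Non-adherence may therefore be included. Its covariates would still be sex, age and baseline HbA1c, not baseline adherence.

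**The gain may be negligible.** This stands as a possibility. In newly diagnosed patients, baseline adherence may reflect a short medication history and predict weakly. A correlation of 0.6, at which the gain would be about 14 to 15 points, should not be used as a headline. With 50% at baseline and 30% at follow-up, φ cannot exceed √(0.3/0.7) = 0.65.

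**Conclusion.** The point holds as one of efficiency and of bias conditional on imbalance. No stated comparison of adherence or knowledge uses the outcome's own pre-randomisation value.

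Two stronger readings are tempting, and neither is supported. The first is that the named tests are invalid: under randomisation they keep their level (4.4% to 4.6% simulated). The second is that a baseline imbalance passes in full into the relative risk and p value: it does so only in proportion to the correlation, and hardly at all at 0.2.

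For non-adherence the size is about 0, 3 and 10 points of power at correlations 0, 0.3 and 0.5, and similar for a knowledge score. These figures rest wholly on the assumed rates, effect sizes and correlations. The change is still worth making, because the possible gain is material and the possible loss is under 1 point.

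**What to change.** Under Data analysis:

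- State the scale of each outcome: the cut-off for non-adherence, and whether knowledge is a score or a category.
- **Non-adherence:** make the main comparison a relative risk adjusted for, or Mantel-Haenszel stratified by, baseline adherence status.
- **Knowledge as a score:** use a linear model of the 6-month score on arm and baseline score. **As a category:** stratify by baseline category.
- Keep the chi-square or Fisher result as the supportive unadjusted analysis.
- Add a simple rule for a missing baseline value, such as a separate missing-baseline category. Few should be missing, since the interview precedes allocation.

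The cost is wording only, with no new data or visits. The change should be fixed before the 6-month data are compared by arm.
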